### Statistical Considerations

Modest reductions in BMI *z* score (0.01-0.15) in adolescents have been associated with improvements in several cardiovascular risk factors and are considered to be clinically meaningful [64]. The population SD for this power calculation was obtained from a contemporary Australian RCT in adolescents [65]. To test for a change in BMI *z* score of 0.15 (SD 0.27) [65] in the intervention group at six-months, compared with the control group, for 80% power (type I error=5%, two-sided test), 1:1 randomization, and accounting for a conservative 30% dropout-rate based on a recent systematic literature review [66], we will require 150 participates (75 participants per group).

Baseline demographic characteristics, attrition rates, and the average number of text messages sent and received for participants will be tabulated and compared using descriptive statistics. Categorical variables will be summarized using totals numbers and percentages. Continuous variables will be summarized using mean and standard deviation for normally distributed data, or median and interquartile range for data that are not normally distributed. The baseline characteristics of completers and noncompleters will be compared to examine attrition bias, using two-tailed *t* tests for continuous variables and chi-square tests for categorical variables. Actigraph GT3X+ accelerometer data will be captured in 1-15 second epochs to capture the intermittent activity patterns of adolescents and downloaded using the ActiLife software into an excel spreadsheet. Time spent in different physical activities will be evaluated by classifying the intensity level using count thresholds specific to adolescents [54,55].

The primary analysis will include all available participant data and will be performed at the end of the study after all the data has been collected. The analysis of the primary and secondary outcomes will be conducted according to the intention-to-treat principle. Continuous outcomes will be analyzed at six- and twelve-months using analysis of covariance (ANCOVA), adjusting for baseline measurement of the outcome, gender, and recruitment site/strategy. Categorical outcomes will be analyzed at six- and twelve-months using log-binomial regression and adjusting for baseline measurement of the outcome, gender, and recruitment site/strategy. Planned subgroup analyses will investigate interactions between treatment and subgroups, including categories of age, socioeconomic status, and ethnicity, to explore trends for future studies. A significance level of 0.05 will be used. All analyses will be undertaken using SAS version 9.4 (SAS Institute Inc, Cary, North Carolina, United States).

Process evaluation data, including questionnaire data, interview data, and text message management data, will be analyzed using mixed methods. Descriptive analysis will be used to examine questionnaire data and software analytics. Interviews will be conducted by a trained qualitative interviewer, digitally recorded and transcribed. Interview data will be analyzed thematically, and coding based on emergent themes using the NVIVO Software program, version 12 (QRS International Pty Ltd, Victoria, Australia).

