### Randomization and Blinding

After obtaining written informed consent from adolescents and their parents or guardians (if <18 years old) and completing the baseline assessment, the research assistant will enter the data into a secure web-based database. Then randomization will occur via a centralized, computerized randomization program in a uniform 1:1 allocation ratio (control: intervention). Randomization is based on a permuted randomized block design, where the strata are gender, age, and recruitment site. The randomized block method contained block sizes of 2 and 4 in a ratio of 2:1 to minimize imbalance in small strata groups. A randomization list was generated by an independent statistician using RandomiseR package [33] within the R computing environment (The R Foundation, Vienna, Austria). For each participant, the computer system automatically produces a study identification number, which will be used on all study documents. On the following Monday, after the baseline visit, the computer system automatically sends the assigned text message program to the participant. Therefore, the researcher conducting all face-to-face assessments remains blind to the study allocation. As an additional precaution and for safety purposes, there will be an independent, unblinded researcher monitoring all incoming text messages.

A 20% (30/150) subsample of participants will be randomly assigned to wear an accelerometer for seven days to validate the self-reported physical activity questionnaire. These participants will receive a second layer of randomization, which will be nested within each treatment arm at a ratio of 1:5. A total of 15 participants with accelerometers will be in the text message intervention group, and 15 participants will be in the control group.

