### Data Collection and Study Outcomes

The in-person follow-up assessments will occur at the end of the six-month intervention period and the end of the six months post-intervention (twelve months from baseline). The primary outcome, secondary outcomes, and their assessments are presented in Table 2. The primary outcome is a change in BMI *z* score (units BMI is above or below average for age- and sex-specific reference values) measured using calibrated stadiometer and electronic scales. BMI is calculated as weight (kg)/[height (meters)^2^]. Bodyweight and height will be measured to the nearest 0.1 kilogram and 0.1 centimeter, respectively, at each assessment time point by the research assistant, who is blinded to participant allocation and is using a standardized protocol [47]. Waist-to-height ratio will be measured to the nearest 0.1 centimeter using a nonstretch plastic waist measurement tape, midway between the iliac crest and the lowest rib, and a calibrated stadiometer.

**Table 2 table2:** Description of TEXTBITES study outcomes and assessments.

Outcome		Assessment

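### Age is a randomisation stratum but is left out of the outcome models, and the site stratum is replaced by an undefined site/strategy term; the likely cost is mild conservatism, probably small for BMI z score

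*Protocol article*

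**What the plan says.** Protocol article, Randomization and Blinding: "Randomization is based on a permuted randomized block design, where the strata are gender, age, and recruitment site". The blocks are small, with "block sizes of 2 and 4 in a ratio of 2:1".

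Protocol article, Statistical Considerations: continuous outcomes at six and twelve months go into an ANCOVA, "adjusting for baseline measurement of the outcome, gender, and recruitment site/strategy". Categorical outcomes get "log-binomial regression and adjusting for baseline measurement of the outcome, gender, and recruitment site/strategy". The covariate list is the same both times. Age enters the analysis only through exploratory "interactions between treatment and subgroups, including categories of age, socioeconomic status, and ethnicity".

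Protocol article, Data Collection and Study Outcomes: the primary outcome is expressed as "units BMI is above or below average for age- and sex-specific reference values".

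**The concern.** Two of the three stratification factors reach the models in some form and the third does not, with no explanation. Stratified blocks force the arms to be similar in age. If age is related to the outcome, that balance makes the treatment estimate less variable. A linear model without age does not see this: it leaves the age variation in its residual and reports a standard error that is too large. The confidence interval is then wider than it need be and some power is lost, in a trial that expects only about 52 evaluable participants per arm.

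The second mismatch is the site/strategy term. Randomisation used recruitment site. Study Design speaks separately of a log of recruitment strategies and lists clinic referral and several kinds of community advertising. A covariate that may mean either one, or a mixture, need not coincide with the stratum and leaves a choice open in the primary model.

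**Working it through.** **Inputs.** From Statistical Considerations: difference 0.15, SD 0.27, two-sided 5% test, 80% power, 1:1 allocation, 30% dropout, 150 participants (75 per group). Not in the article: the share of residual variance that age explains once baseline, gender and site are in the model (partial R²). It is assumed here to range from 0 to 0.20. The SD of 0.27 is taken as the residual SD without age.

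**The plan's own figure.** Normal approximation: n per arm = 2 × (1.960 + 0.842)² × 0.27² / 0.15² = 50.9, so 51. Then 51/0.70 = 72.9, so 73 per arm and 146 in total. The t-test version needs 52 per arm; 52/0.70 = 74.3, so 75 per arm and 150 in total. The stated sample size reproduces and is not in question.

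**Formula check, assuming perfect age balance.** Completers per arm: 75 × 0.70 = 52.5. SE = 0.27 × √(2/52.5) = 0.0527. Write k = √(1 − R²).

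- Without age, the model reports SE but the estimate truly varies with SE × k. Actual type I error = 2Φ(−1.96/k). Power = Φ((0.15/SE − 1.96)/k).
- With age, the model reports SE × k. Power = Φ(0.15/(SE × k) − 1.96).

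| Assumed partial R² | SE with age | Type I error without age | Power without age | Power with age |
|---|---|---|---|---|
| 0 | 0.0527 | 5.0% | 81.2% | 81.2% |
| 0.02 | 0.0522 | 4.8% | 81.5% | 82.0% |
| 0.05 | 0.0514 | 4.4% | 81.8% | 83.2% |
| 0.10 | 0.0500 | 3.9% | 82.5% | 85.1% |
| 0.20 | 0.0471 | 2.8% | 83.9% | 88.9% |

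**Simulation check.** The formulas ignore dropout and unfinished blocks, both of which loosen the balance. So 4,000 trials per setting were simulated with N = 150, stratified blocks of 2 and 4 in a 2:1 ratio, 30% random dropout, and ANCOVA with and without age. Two age groups and two sites were assumed. Monte Carlo error is about 0.35 points for type I error and 0.65 points for power.

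| Assumed partial R² | Model SE / empirical SE, without age | Type I error without age | Power without age | Power with age |
|---|---|---|---|---|
| 0 | 0.0531 / 0.0532 | 5.0% | 79.1% | 79.0% |
| 0.02 | 0.0533 / 0.0531 | 4.4% | 79.7% | 80.5% |
| 0.05 | 0.0531 / 0.0514 | 4.4% | 79.8% | 81.5% |
| 0.10 | 0.0531 / 0.0514 | 4.7% | 80.2% | 83.3% |
| 0.20 | 0.0532 / 0.0493 | 3.3% | 81.6% | 87.3% |

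**Reading.** At a partial R² of 0.05 to 0.10, adding age gains 1.3 to 2.6 points of power by formula and about 1.7 to 3.0 by simulation. At R² = 0 the model without age is correctly calibrated, and adding age changes power by only 0.1 point. In no setting does the type I error without age exceed 5% by more than simulation error. All of this concerns a difference in means; nothing was computed for the log-binomial models.

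**The case against.** The strongest reply is that the primary outcome is already standardised for age and sex and that its baseline value is a covariate. Most of what age could explain may therefore be gone, and a partial R² near zero is plausible. This stands, and it is why the effect on BMI z score should be called probably small. The pull of age is less clearly removed for secondary outcomes such as physical and sedentary activity, sleep, self-esteem and depression. The article does not describe these as age-standardised, and participants span 13 to 18 years.

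Second, even where age matters the error is in the safe direction, and power stays close to the planned 80%. This also stands.

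Third, site and strategy may largely coincide, since Study Design names the clinic both as a site and as a referral route. Adjusting for a pre-randomisation variable that was not a stratum is not an error in itself, and the slash may be condensed wording for something the full protocol defines. This is partly right. The complaint is only that the term is ambiguous and need not equal the stratum.

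Fourth, a separate analysis plan may settle the covariates. But the article does not leave the list open. It states the same closed list twice, and a plan that follows it would omit age.

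**Conclusion.** The mismatch holds: age is a stratum and is absent from both stated models, and the site stratum is replaced by an undefined term. Its consequence is conditional. If age is prognostic given the baseline value, gender and site, the ANCOVA is mildly conservative. For BMI z score the loss is nil at R² = 0 and about 1 to 3 points of power at an assumed partial R² of 0.05 to 0.10. The loss for secondary outcomes could be larger but cannot be sized from the article.

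A reader might infer more: that the primary standard error is certainly too wide, or that the primary confidence interval and p value are invalid. The article does not support this. It gives no figure for the prognostic strength of age, the outcome scale already refers to age, and leaving age out causes neither bias nor type I error inflation. A reader might also carry the standard-error argument over to the log-binomial models. The linear-model reasoning does not transfer automatically, so for those models only the mismatch is shown, not its size.

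Severity: minor.

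**What to change.** In Statistical Considerations, for continuous and categorical outcomes alike, replace the covariate list with the baseline value of the outcome plus the stratification factors as randomised: gender, age stratum and recruitment site. Use the age categories and site codes of the randomisation list, and drop the site/strategy wording. If the team prefers to leave age out, it should say why. Recruitment strategy, if of interest, can be defined and used in a sensitivity analysis.

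The cost is one sentence, settled before unblinding, and an extra model term. No new data are needed, because age and site are already recorded for randomisation.

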### Dissemination

The study findings will be disseminated via peer-reviewed publications and presentations at national and international conference meetings. Results will also be presented and communicated appropriately to relevant adolescent and consumer groups.

### Ethical Approval and Consent to Participate

Formal ethical approval for this study has been obtained from the Sydney Children’s Hospitals Network Human Research Ethics Committee (approval number HREC/18/SCHN/374). The current protocol version is Version 2.0 (March 20, 2019). Written and informed consent will be collected from all participants and their parents/guardians (if they are <18 years old). The study is sponsored by the University of Sydney and managed by staff based there. The sponsor has no role in the study design, the collection, management, analysis, and interpretation of data, the writing of the findings, or the decision to submit the findings for publication. The design and conduct of the study will be overseen by a steering committee (authors). This study will adhere to the Australian National Health and Medical Research Council ethical guidelines for human research, and the study will follow the Consolidated Standards of Reporting Trials guidelines [67].

## Results

Recruitment for the trial will start in December 2019 and is expected to run until the end of 2020. Data collection is expected to be complete by December 2021, and dissemination of trial results is planned after that. The results on the primary outcome are expected to be ready during early 2022.

## Discussion

### Primary Findings

The study will evaluate an innovative means of delivering a simple obesity prevention program to adolescents who are overweight and are at risk of obesity using an RCT. It is hypothesized that the intervention group will see improvements in primary and secondary outcomes compared to control post-intervention (six-months) and at follow-up (twelve-months). If effective, this study will inform translational research to improve BMI and lifestyle outcomes for adolescents, and to prevent the transition to obesity in young adulthood. Results of the process evaluation will assess the barriers and enablers to widespread implementation of the text message program, with the ultimate goal of providing adolescents with age-appropriate, evidence-based, and accessible obesity prevention services.

The simple and innovative text message program addresses a critical gap in obesity prevention for adolescents, given their risk of future chronic diseases. Text messages are an appropriate and accessible intervention delivery modality for this population group. The benefit of text messages is that they do not require an internet connection to receive, offer an interactive modality to communicate with health professionals, can be delivered with minimal personnel, and may provide a socially equitable intervention for most adolescents. As such, text message interventions show the potential to reduce socioeconomic disparities in health care and deliver a scalable, low-cost intervention to a wide population. To date, there have been only eight RCTs investigating text messages for obesity prevention or management in adolescent populations [30,68-74]. The interventions were mostly multicomponent mobile health interventions, and there was limited process evaluation data to help understand the effects of the text message component. Taken together, currently, there is limited high-quality research investigating obesity prevention interventions delivered via text message for adolescents. Hence, the TEXTBITES study aims to address this research gap.

### Conclusion

This study will test the effectiveness of a six-month text message intervention to improve BMI and lifestyle outcomes for adolescents who are overweight and at risk of obesity. If effective at improving BMI and lifestyle outcomes, the results will provide evidence to inform future practice and community initiatives to promote obesity prevention behaviors for adolescents, and ultimately be translated to help all adolescents nationally and internationally.

## Abbreviations

ACAES: Australian Child and Adolescent Eating Survey
ASAQ: Adolescent Sedentary Activity Questionnaire
ANCOVA: analysis of covariance
BMI: body mass index
CESDR-10: Centre for Epidemiologic Studies Depression Scale-Revised
EDE-Q: Eating Disorder Examination questionnaire
PedsQL: Pediatric Quality of Life Inventory
PSQI-Short: Pittsburgh Sleep Quality Index Short
RCT: randomized controlled trial
SMS: short message service
TEXTMEDS: TEXT messages to improve MEDication adherence and Secondary prevention
TEXTBITES: TEXT message Behavioral Intervention for Teens on Eating, physical activity, and Social wellbeing
